#### Statistical methods  – analysis population and missing data

All main analyses will be conducted as intention-to-treat analyses, including all randomised participants, regardless of protocol adherence. Participants will be analysed as randomised. To create a full analysis dataset for the intention-to-treat analyses, missing outcome data will be imputed using multiple imputations based on the variables of all previous scores in the relevant outcome, age, sex and allocation.

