### Outcomes

#### Primary outcome

The primary outcome will be the change in the patient-reported outcome (PRO) score SPADI [43]. SPADI is a widely used shoulder-specific PRO [44], considered one of the most responsive shoulder PROs [45–48], with a minimal clinical important difference (MCID) of 8 to 13 points [45, 48] and a high standardised response mean of 1.38. The SPADI is easy and fast to complete [48] and, in a recent systematic review [49], it was highlighted as one of three PROs for patients with rotator cuff disease for which the psychometric properties are supported by most strong or moderate evidence.

Baseline values for the primary outcome will be collected from patient records, and passed on by the treating physician to the primary investigator, as completion of the SPADI questionnaire is an integral part of the medical examination. Primary outcome data will be further collected at follow-up weeks 5, 10 and 16, with the main analysis conducted for changes from baseline to 16 weeks follow-up, reported as the difference in mean change between groups.

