### Procedures and data collection methods

At baseline, after written consent is signed and before randomisation, all baseline assessments (Fig. 1) will be conducted by clinical physiotherapists who are trained in all assessment procedures and mutually aligned in order to improve the quality of data. All post-allocation assessments (week 5, 10 and 16) will be performed by the same group of testers in order to secure consensus regarding the instructions in questionnaires and conduction of tests. Participants will be instructed not to take any pain medication during the 8 hours prior to any assessment. Outcome assessors will also be trained in counselling for adherence to follow-up testing (to facilitate retention) and avoidance of disclosing allocation in a uniform manner. The study instruments are all described in detail in Additional file 7.

In general, once a participant is enrolled, every reasonable effort will be made to collect all outcomes for that participant, regardless of any deviations from the intervention protocol. Participants will receive text-message reminders for all scheduled follow-up appointments. The weekly text-messages with standardised questions regarding exercise time will also ensure that participants keep in mind their participation in the study. If participants do not attend their scheduled follow-up assessment, they will be contacted and offered to re-schedule to another date. If a participant should withdraw consent to follow-up assessments, the participant is offered the option to continue with the assessment of PROs.

Reasons for non-adherence to add-on intervention will be recorded by the investigator providing the intervention, either at the intervention visits or by phone if the participant does not come to the scheduled appointment. Reasons for non-retention will be recorded by the outcome assessor if this participant withdraws during a follow-up session, or by the primary investigator in a telephone interview.

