### Statistical methods – outcomes

For the primary end-point, namely SPADI score after 16 weeks, and for all continuous secondary outcomes listed in Table 2, a constrained linear mixed model (cLMM) will be applied in order to compare the change from baseline to 16 weeks in the IG to that in the CG. The model will contain the outcome at 16 weeks as the dependent variable, treatment group (IG or CG) as the main effect and both baseline score and any additional follow-up measurements as repeated measurements, to estimate the differences in mean change between groups and corresponding 95% confidence intervals (95% CI) (Table 3). The covariance structures will be selected based on the MAICE procedure [57].

**Table 2 Tab2:** Variables, outcome measures and methods of analysis

Variable/outcome	Hypothesis	Outcome measure	Methods of analysis
Primary outcome	Intervention improved outcome		
SPADI change Δt_0_-t_3_		Score 0–100 (continuous)	cLMM
Secondary outcomes	Intervention improved outcome		
Abd. MVC change Δt_0_-t_3_		Nm/kg (continuous)	cLMM
Ext. rot. MVC change Δt_0_-t_3_		Nm/kg (continuous)	cLMM
Abd. total ROM change Δt_0_-t_3_		Degrees (continuous)	cLMM
Pain last week change Δt_0_-t_3_		NRS 0–10 (continuous)	cLMM
EQ-5D change Δt_0_-t_3_		Index value (continuous)	cLMM
Global impression of change, at t_3_		% much improved/fully recovered (binary)	χ^2^ test
Pain sensitisation Δt_1_-t_3_			
Temporal Summation of Pain		VAS increase (continuous)	cLMM
Conditioned Pain Modulation		kPa increase (continuous)	cLMM
Pain Pressure Threshold		kPa (continuous)	cLMM
Scapular involvement			
SAT		% positive (binary)	χ^2^ test
SDT		% positive (binary)	χ^2^ test
Subgroup analyses			
Scapula involvement (SAT and SDT yes/no)	Dysfunction modifies the effect of intervention	SPADI score, abduction MVC and external rotation MVC (continuous)	cLMM with interaction term
Central sensitisation (TS and CPM high vs. low)	CS modifies the effect of intervention	SPADI score, abduction MVC and external rotation MVC (continuous)	cLMM with interaction term
Sensitivity analyses	Intervention improved outcome	Primary outcome	
Per protocol analysis			cLMM
Adjusting for baseline			cLMM

*cLMM* constrained linear mixed model, *EQ-5D* EuroQol 5D-3 L, *MVC* maximum voluntary contraction, *Nm/kg* Newton meter per kilo body weight, *ROM* range of movement, *SAT* scapula dysfunction, *SDT* scapula dyskinesia, *SPADI* Shoulder Pain and Disability Index, VAS visual analogue scale

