**Table 3 Tab3:** Outcomes (Mean, SD)

	Week 0		Week 5		Week 10		Week 16	
	IG	CG	IG	CG	IG	CG	IG	CG
SPADI score								
Abduction MVC								
External rotation MVC								
Abduction ROM								
Pain last week								
QoL (EQ-5D)								

*CG* control group, *IG* intervention group, *MVC* maximum voluntary contraction, *QoL* quality of life, *ROM* range of movement, *SPADI* Shoulder Pain and Disability Index

Mean scores and corresponding 95% CIs will be reported for all outcome time-points (t_0_, t_1_, t_2_ and t_3_) (Table 3). Within group changes between all outcomes assessment time-points (t_0_-t_1_, t_1_-t_2_ and t_2_-t_3_), and between baseline and last assessment (t_0_ and t_3_), and corresponding 95% CI, will be reported (Table 4). Finally, differences in within group changes between all outcomes assessment time-points (t_0_-t_1_, t_1_-t_2_ and t_2_-t_3_) and the corresponding 95% CIs will be reported (Table 5). Results from the repeated measures analysis with SPADI score as outcome will be visualised as illustrated in Fig. 2.

**Table 4 Tab4:** Within group change scores (95% CI)

	Week 0–5		Week 5–10		Week 10–16		Week 0–16	
	IG	CG	IG	CG	IG	CG	IG	CG
SPADI score								
Abduction MVC								
External rotation MVC								
Abduction ROM								
Pain last week								
QoL (EQ-5D)								

*CG* control group, *IG* intervention group, *MVC* maximum voluntary contraction, *QoL* quality of life, *ROM* range of movement, *SPADI* Shoulder Pain and Disability Index

**Table 5 Tab5:** Between group difference in change scores (95% CI)

	Week 0 to 5 (95% CI)	Week 5 to 10 (95% CI)	Week 10 to 16 (95% CI)	Week 0 to 16 (95% CI)
SPADI score				
Abduction MVC				
External rotation MVC				
Abduction ROM				
Pain last week				
QoL (EQ-5D)				

*CG* control group, *IG* intervention group, *MVC* maximum voluntary contraction, *QoL* quality of life, *ROM* range of movement, *SPADI* Shoulder Pain and Disability Index

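### Imputing a missed week-5 or week-10 score from earlier scores only ignores the patient's own later score; if such gaps are common, the week 5–10 and 10–16 intervals come out too wide.

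*Protocol article*

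**What the plan says.** Under the heading on analysis population and missing data, the article states: "To create a full analysis dataset for the intention-to-treat analyses, missing outcome data will be imputed". The predictors are listed in full: "multiple imputations based on the variables of all previous scores in the relevant outcome, age, sex and allocation". Later scores are not among them. The rule is not limited to week 16 or to patients who drop out for good.

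Under Primary outcome: "Primary outcome data will be further collected at follow-up weeks 5, 10 and 16". Under Procedures and data collection methods, a missed visit does not end follow-up. The article promises that "every reasonable effort will be made to collect all outcomes for that participant, regardless of any deviations from the intervention protocol", and adds: "If participants do not attend their scheduled follow-up assessment, they will be contacted". A patient can therefore miss a middle visit and be measured at a later one.

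Under Statistical methods – outcomes, the mixed model takes "both baseline score and any additional follow-up measurements as repeated measurements", and the article commits to the step-by-step contrasts: "differences in within group changes between all outcomes assessment time-points (t_0_-t_1_, t_1_-t_2_ and t_2_-t_3_) and the corresponding 95% CIs will be reported". Table 4 has the matching within-group changes. Both tables cover SPADI, two strength measures, range of movement, pain and EQ-5D.

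**The concern.** Conditioning on earlier scores is enough when missing data are monotone, because a patient who has left has no later scores. It is not enough for a gap in the middle. A missing week-10 score is then drawn from weeks 0 and 5, and a missing week-5 score from week 0, although week 16 (or weeks 10 and 16) may be on file.

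The omitted score is the other half of the change being estimated. Given the earlier scores, the imputed value is independent of it. The correlation between the two visits is therefore pulled down and the variance of the change is pushed up. At stake are the intervals for weeks 5–10 and 10–16 in Tables 4 and 5. If attendance at the middle visit also depends on later outcome differently in the two arms, the between-group estimate for those periods is affected too.

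**Working it through.** **Inputs from the protocol article (Sample size).** 100 per arm; SD of the week 0–16 SPADI change 19.5; difference 10; two-sided 5%; power 95%. Check: n per arm = 2 × (1.960 + 1.645)² × 19.5² / 10² = 98.8, so 99 per arm and 198 in total, in line with the planned 200. The article gives no figure for intermittent gaps or for correlations between visits.

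**Assumptions.** Correlations for visits one, two and three apart: 0.75, 0.65, 0.525 (set A) or 0.85, 0.75, 0.65 (set B). The SD at each visit is set so that the week 0–16 change has SD 19.5. For set A: 19.5 / √(2 × (1 − 0.525)) = 20.0, variance 400.3. Gap rates are 5%, 10% and 20%.

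**Step 1: mechanism, set A, missing week 10.** The covariance of weeks 10 and 16 given weeks 0 and 5, in units of the variance, is 0.75 − [0.65×0.525 + 0.75×0.65 − 0.75×(0.65×0.65 + 0.75×0.525)] / (1 − 0.75²) = 0.75 − 0.495 = 0.255. The previous-only rule sets this to zero.
- Variance of the week 10–16 change with real scores: 2 × (1 − 0.75) × 400.3 = 200.
- With a previous-only imputed week 10: 200 + 2 × 0.255 × 400.3 = 404, about double.
- Week 10–16 correlation in the completed data at 20% gaps: 0.75 − 0.2 × 0.255 = 0.70.

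**Step 2: effect on the intervals, gaps completely at random.** Simulation: 1,500 trials per row, 15 imputations, Rubin's rules. The change was regressed on arm and baseline, as a stand-in for the constrained mixed model; age and sex were left out. Excess = reported SE / empirical SE − 1.

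| Contrast, set | Gaps | Empirical SE | Reported SE | Excess | Coverage | CI width, previous only | CI width, with later scores |
|---|---|---|---|---|---|---|---|
| 10–16, A | 5% | 2.05 | 2.07 | 1% | 94.8% | 8.18 | 7.92 |
| 10–16, A | 10% | 2.03 | 2.17 | 7% | 96.4% | 8.57 | 8.07 |
| 10–16, A | 20% | 2.17 | 2.38 | 10% | 96.7% | 9.43 | 8.48 |
| 10–16, B | 5% | 1.84 | 1.89 | 3% | 95.5% | 7.45 | 7.13 |
| 10–16, B | 10% | 1.88 | 2.00 | 6% | 96.5% | 7.89 | 7.27 |
| 10–16, B | 20% | 2.06 | 2.22 | 8% | 96.5% | 8.79 | 7.61 |
| 5–10, A | 5% | 2.00 | 2.09 | 5% | 96.0% | 8.23 | 7.97 |
| 5–10, A | 10% | 2.07 | 2.19 | 6% | 96.3% | 8.65 | 8.14 |
| 5–10, A | 20% | 2.21 | 2.40 | 9% | 97.4% | 9.51 | 8.54 |
| 5–10, B | 5% | 1.84 | 1.89 | 3% | 95.3% | 7.45 | 7.12 |
| 5–10, B | 10% | 1.84 | 2.00 | 9% | 97.2% | 7.89 | 7.27 |
| 5–10, B | 20% | 1.97 | 2.23 | 13% | 96.7% | 8.83 | 7.63 |

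Further runs for weeks 10–16, under other assumed values (SDs 18–22, correlations 0.45–0.80 in most), gave an excess of 1–3% at 5% gaps, 5–11% at 10% and 14–16% at 20%. All runs together: 1–5%, 5–11% and 8–16%. The empirical SE carries Monte Carlo error of about 1/√(2 × 1500) = 1.8%, so small excesses are imprecise. The width ratios are steadier: 3–5% wider than with later scores at 5% gaps, 6–9% at 10%, 11–16% at 20%.

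**Step 3: bias in the between-group contrast.**
- Gaps random, or depending on the later score alike in both arms: bias at most about 0.1 points.
- Gaps depending on the later score in opposite directions by arm, base rate 15% (assumed): bias 1.6–1.8 points and coverage 91–92% for both contrasts. A separate run gave about 1.2–2.2 points. With later scores in the imputation model, bias is within 0.05 points and coverage about 95%.

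**The case against.** The rule suits the analysis it mainly serves. The main analyses are week 0 to 16, or the outcome at week 16. For a missing week-16 score the earlier scores are all the other scores there are, and the same is true for permanent dropout, the only kind the Sample size section plans for. The article does not say whether Tables 4 and 5 use the imputed data. Reminders, contact after a missed visit and rescheduling should keep middle gaps few, and at 5% the effect is hardly visible. All of this stands. It makes the point conditional but does not remove it, because the rule is written for all missing outcome data and aims at a full dataset.

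Three stronger readings are tempting and are not supported:
- **That the step-by-step intervals are simply wrong.** They are affected only if enough patients miss a middle visit and return, and under random gaps they err on the conservative side. The 20% row is an assumed rate of middle gaps, not the 20% dropout in the Sample size section.
- **That the between-group contrasts are biased whenever skipping a visit relates to later outcome.** The dependence must also differ by arm. The intervention arm has extra appointments at weeks 5 and 10, so this is conceivable, but nothing in the article shows it.
- **That the primary result is at risk.** When week 16 is observed, an imputed middle visit has essentially no bearing on the week 0–16 contrast.

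**Conclusion.** The point holds as a minor, conditional one. The imputation rule fixes a set of predictors that discards observed data for patients with a gap at week 5 or 10. If Tables 4 and 5 use the imputed data and gaps are random, the week 5–10 and 10–16 intervals are too wide: negligibly at 5% gaps, and by roughly a tenth at 20%, with coverage up to about 97–98%. Bias of 1–2 SPADI points in these between-group contrasts needs arm-dependent missingness tied to the later score. These sizes rest on assumed correlations, gap rates and missingness mechanisms, none of which the article gives, and on a regression stand-in for the mixed model. The direction rests only on the wording of the rule.

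**What to change.** In the section on analysis population and missing data, replace the restriction to earlier scores with all other observed scores of the same outcome, whether earlier or later, and keep age, sex and allocation. In practice the visits are imputed together, by a joint normal model or fully conditional specification. For permanent dropout the set of observed predictors stays the same. State also whether Tables 4 and 5 use the imputed data.

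The cost is a few words. SAS and SPSS, the packages the article names, can both do this, and no new data are needed.

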### Harms

Adverse events will be defined in this context as any unintended, unfavourable findings, symptom or illnesses that occur during the assessment or the add-on intervention, whether it can be attributed to the assessment or not. Adverse events will be recorded in part by the patient as a spontaneous recording during assessment and by open questioning.

Acute exacerbations of shoulder symptoms will be recorded by the primary investigator (MC) and, as a safety precaution, in case a medical evaluation is required, the participant will be referred to the Medical Advisor (PH). Patients in the intervention group experiencing exacerbations lasting more than 1 week will be referred to the Medical Advisor (PH) and evaluated if further medical care is needed.

Serious unexpected side effects or serious adverse events will be reported to the Capital Regional Ethics Committee in Denmark within 7 days after sponsor or the primary investigator has become aware of the incident. Serious adverse events will be categorised according to the definitions established by the United States Food and Drug Administration [59] and will be assessed by the primary investigator for possible relations with the assessment and/or intervention to consider whether there is a reasonable possibility that the adverse event can be caused by either.

No audits are planned.

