In the current study, we aim to increase the received dose of strengthening exercises aimed at the rotator cuff muscles in patients with long-lasting SIS without aggravating their symptoms and with minimal risk of adverse events. To achieve this, the intervention will start with exercises using low relative resistance but high volume (number of sets per session and frequency of sessions). This approach is also relevant, as resistance training with low intensity/resistance, high frequency and approximately 3–4 sets per muscle group is associated with the highest gains in muscle strength in untrained individuals [21]. All sets are to be continued to failure, as this maximises the gain in local muscle endurance [22]. Furthermore, the low resistance will minimise pain during exercises and protect the muscle from overload injuries, ensuring that all patients are able to complete the programme.

The focus of exercises is on isometric holds and slow dynamic strengthening with a long time under tension (TUT). A high TUT is achieved through exercises with a low contraction velocity and the inclusion of an isometric component to increase the exercise stimulus without increasing external resistance; this in turn reduces the peak load on the involved, and possibly damaged [16], muscles and tendons. Thus, exercises become safer and less painful, which again will allow patients to actually adhere to the exercise intervention. Furthermore, the isometric part will be performed with the shoulder in approximately 30–45 degrees of scaption, the position in which the compression forces on the supraspinatus muscle and tendon are lowest [23, 24]. Exercises will mainly focus on external rotation and abduction, functions in which both supraspinatus and infraspinatus muscles are highly active [25].

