### Interventions

Both groups will receive usual care consisting of an offer of referral to general rehabilitation in the municipal clinic under the Danish health Act § 140, sometimes with the option to instead choose a private physiotherapy clinic, partly at their own expense. The referral is standard procedure when a patient with SIS is considered to have a medically justified need for general rehabilitation, as identified during the examination at the orthopaedic outpatient department (secondary care unit). This procedure is based on the Danish National clinical guideline on diagnostics and treatment of patients with selected shoulder disorders [10], as exercise therapy is recommended as first line of treatment for SIS.

In the context of this study, usual care includes all treatment received by a patient during the time between baseline and follow-up, except that included in ‘Strengthen your Shoulder’. Therefore, usual care might include a range of treatment modalities including advice, stretching, exercises, manual therapy, massage, acupuncture and electrotherapy at the discretion of the treating physiotherapist and doctor. A description of usual care following the TIDieR guidelines [33] is included in Additional file 2.

Patients in the intervention group will, in addition to usual care, receive instructions regarding a home-based, progressive, high volume resistance-training programme immediately after randomisation. Instructions in the exercises are provided at baseline (week 0) and after 2, 5, 10 and 16 weeks. The exercise programme has been developed in cooperation with a team of experts with extensive knowledge of both exercise physiology and rehabilitation and training of patients with shoulder disorders (MC, TB, KT and MR). The design of the exercises, and their progression, is based on the relevant literature regarding exercise physiology, shoulder biomechanics and strength training principles for both healthy people and patients with shoulder disorders. A standard protocol for individual adaptation of the programme based on pain response is part of the intervention.

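### The adverse event definition covers time on the add-on, which only one arm receives, so a count by arm would tend to show more events in the intervention group

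*Protocol article*

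**What the plan says.** All of the following is in the protocol article.

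- **Definition (Harms).** An adverse event is "any unintended, unfavourable findings, symptom or illnesses that occur during the assessment or the add-on intervention". A further clause makes this apply "whether it can be attributed to the assessment or not".
- **Collection (Harms).** Events are "recorded in part by the patient as a spontaneous recording during assessment and by open questioning". No arm is named.
- **Exacerbations (Harms).** "Acute exacerbations of shoulder symptoms will be recorded by the primary investigator", again with no arm named. The next rule does name one: "Patients in the intervention group experiencing exacerbations lasting more than 1 week will be referred to the Medical Advisor".
- **Serious events (Harms).** These are "assessed by the primary investigator for possible relations with the assessment and/or intervention". Usual care is not mentioned as a possible cause.
- **Who has the add-on (Interventions).** "Patients in the intervention group will, in addition to usual care, receive instructions regarding a home-based, progressive, high volume resistance-training programme". The programme runs for 16 weeks, with instruction appointments at weeks 0, 2, 5, 10 and 16.
- **Assessments (Procedures and data collection methods; Blinding).** Baseline testing comes before randomisation. Both arms are then assessed at weeks 5, 10 and 16 by blinded assessors. Intervention providers are not blinded.
- **Safety aim (Dose selection).** The exercise dose is to be raised "without aggravating their symptoms and with minimal risk of adverse events".

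**The concern.** One of the two circumstances that make an occurrence an adverse event exists in one arm only. A control patient can never be on the add-on, so only the assessment limb of the definition can apply to that patient. The intervention group is also seen more often, by a provider who knows the allocation, and so has more occasions on which an event can come to light.

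This is a rule that the article states, not a detail it leaves out. Patients with long-lasting shoulder pain may have unfavourable symptoms in either arm. Whether the programme adds to them can be judged from event counts only if both arms are counted in the same way. If they are not, a table by arm can show an excess with the add-on even when there is none. That bears on the safety aim under Dose selection and on the suggestion in the Discussion that an effective programme could easily be added to usual care.

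**Working it through.** The plan gives no figure for harms, so there is none to reproduce. The check sets the passages side by side and counts contacts.

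**1. Contacts after allocation**
- Control: assessments at weeks 5, 10 and 16, which is 3.
- Intervention: the same 3 assessments plus 5 instruction appointments (weeks 0, 2, 5, 10, 16), so 3 + 5 = 8. Weeks 0 (after randomisation) and 2 have no counterpart in the control arm.

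**2. Does the attribution clause repair the definition?** No. It removes the need to show that the assessment caused the event. It does not change when the event must occur.

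**3. What each reading of the definition gives**
- *Both limbs narrow* (test sessions; exercise sessions). Controls have 3 test sessions after allocation. The intervention group has those 3 plus its exercise sessions. Table 1 prescribes 7 × 5 + 3.5 × 5 + 3.5 × 6 = 35 + 17.5 + 21 = 73.5 sessions per patient. Events in those sessions have no equivalent among controls.
- *Assessment narrow, add-on broad* (test sessions; the whole programme). The intervention group has 16 × 7 = 112 days. Controls have 3 visits, or 3/112 = 2.7% of that time if each visit counts as a full day.
- *Assessment broad* (the whole follow-up). The windows match, but the limb about the add-on then adds nothing. The same section also ties spontaneous recording to the assessment and speaks of events being attributable to it, which fits a test visit better than a 16-week period.

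The definition is therefore unequal unless the assessment means all of follow-up, and the article does not say that it does. The extra contacts remain under every reading.

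**4. Does the rest of the section even things out?** In part. Open questioning and the recording of acute exacerbations name no arm. In the other direction, the rule for exacerbations over 1 week names the intervention group only, and relatedness of serious events is judged against the assessment and the intervention. No sentence says how events in controls between visits are to be learned of, or that they count as adverse events.

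**5. Direction and size.** Each inequality found works towards more recorded events in the intervention group. The size cannot be calculated, because it depends on how much open questioning and exacerbation recording pick up among controls.

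**The case against.** The strongest reply has four parts.

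- **Shoulder flares have their own record.** The sentence on acute exacerbations names no arm, while the next rule does. That contrast suggests the recording covers everyone. This stands, and it is a main reason why the size of the bias is unknown.
- **Open questioning takes place at visits that both arms attend.** The exact question and its recall period are details that an article may leave to the full protocol, so their absence is no finding. This also stands. Even so, the stated definition still governs which answers count.
- **Worsening is measured alike in both arms.** SPADI and pain in the last week are collected at weeks 5, 10 and 16, and global impression of change at week 16. Injections and pain medication are recorded too. This stands: aggravation of symptoms has a like-for-like randomised comparison.
- **No test of adverse events between arms is planned.** Neither the objectives nor Table 2 lists one. The point therefore concerns any descriptive table by arm.

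A reader might go further and infer that controls have almost no observation window, that harms are beyond comparison, or that a spurious excess of a given size must appear. The documents do not support this. The contrast of 112 days with a few visits reads one limb broadly and the other narrowly. A near-zero control count would also require that open questioning and exacerbation recording capture nothing in that arm.

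**Conclusion.** The concern holds in a limited form. As written, the definition of an adverse event and the opportunity to detect one differ between the arms, and a count by arm would tend to be biased towards more events in the intervention group. The direction follows from the wording and the visit schedule. The size is unknown.

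The conclusion on the definition rests on reading the assessment as the test visits, which is how the Harms section appears to use the word. If it was meant as the whole follow-up, the definition would be equal and only the difference in contacts would remain. The primary SPADI analysis and the comparison of symptom scores are not affected. The change is worth making because it is cheap, not because the trial's main result is in doubt.

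**What to change.** - Define an adverse event identically in both arms: any unfavourable sign, symptom or illness from randomisation to week 16, whatever its cause.
- Have the blinded assessors ask every participant the same open question, covering the time since the last visit, at weeks 5, 10 and 16.
- Base the table by arm on those reports alone. List events found only at intervention contacts separately, labelled as such.

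The cost is one reworded definition and one standard question at visits that already take place. The downside is a few more recorded events, mainly in controls. The change concerns recording and reporting only and leaves the referral rules as they are.

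The article expects recruitment to end on April 1, 2018, so many participants may already have been followed under the present wording. For them the reporting part can still be applied: tabulate what was recorded at the shared assessments, list the rest apart, and state in the trial report that ascertainment differed by arm.
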